### Patient and public involvement statement

Patient organisations regarding PCa were involved in the design, especially in defining the outcomes, that is, non-inferiority margin. Patients or the public were not involved in the recruitment of participants. However, within this study patients are being recruited for participation. Results will be shared with participants and patient organisations; after dissemination of the results, patient organisations can also further share the outcomes of this study through websites and magazines.

## Ethics and dissemination

###  Ethical approval

The protocol, informed consent form, participant information and amendments are reviewed and approved by the sponsor (the National Health Care Institute and ZonMw). Ethical approval has been obtained from the local accredited Medical Research Ethics Committee (NL83913.091.23, primary approval in December 2023; last approved version 10 July 2025), MREC Oost-Nederland. The approval is valid for all participating centres. Besides the ethical approval for the study, local feasibility was obtained in all participating centres.

### Dissemination

Manuscripts with the results will be published in peer-reviewed medical journals. The data will be stored in a dedicated and secure workspace of the Digital Research Environment (anDREa). Access to the data within the anDREa is available everywhere. The metadata will be published at the certified DANS EASY public archive. In our publications, we will include links to the datasets used for publication.

## Discussion

Currently, the standard of care in intermediate-risk PCa includes RP and RT.^3^ However, there is growing interest among patients and physicians in alternative, organ-sparing approaches such as focal therapy. Our study, ENFORCE focal, is designed to generate high-quality evidence through an RCT comparing focal therapy to the current standard of care. The key strength of this design is the comparison between the groups of therapies rather than a one-to-one comparison of individual therapies, which distinguishes this study from other RCTs on focal therapy.^19^ Therapies in the focal therapy group are selected based on the available clinical experience in the Netherlands. Prostate MRIs are routinely performed in Dutch hospitals, so eligible patients can be referred by non-participating centres to the study sites. We are confident that recruitment of the required number of patients to evaluate (cost-)effectiveness and QoL can be achieved within the planned 2.5-year timeframe. The geographical distribution of including centres will ensure good national coverage within the Netherlands.

Our study is recognised as important for potential treatment options for patients with intermediate-risk PCa and is funded by the programme ‘Potentially Promising Care’ (Dutch: Veelbelovende Zorg) by the National Health Care Institute and ZonMw (ZorgOnderzoek Nederland Medische Wetenschappen). This programme is aimed at funding clinical studies that collect evidence on promising but relatively costly treatments. One of the key objectives of this study under this grant is to contribute to existing evidence of focal therapy and to contribute to the decision-making whether these treatment options will be reimbursed and included in the standard care for intermediate-risk PCa.

We expect several challenges in executing our study. First, in previous studies no differences have been observed between the different focal therapies,^8 14^ but these techniques have not been directly compared within a single study. We aim to gain more insights into potential existing differences between the different modalities. For this aim, we will perform exploratory analyses for the focal therapies versus the radical treatments. Adjustment for centre will not be possible in these analyses since the type of focal therapy is centre-dependent; also the offered standard of care modalities differ between the centres. Furthermore, the different centres may have different perioperative protocols or complications.

Second, another complexity in this study is the difference in follow-up protocols between the treatment arms. In the standard of care arm, PSA is used as the primary follow-up marker. After RP the PSA level is expected to become undetectable within 2 months.^20^ PSA levels in RT drop more slowly compared with RP. No optimal cut-off value has been determined, but in current clinical practice a PSA<0.5 ng/mL is set as a favourable outcome after RT.^21^ However, after focal therapy, PSA monitoring becomes less reliable since the untreated part of the prostate continues to function and produce PSA as before. This necessitates a different follow-up approach for patients in the focal therapy arm. In this trial, we will perform MRI and biopsies as an additional part of the follow-up after focal therapy, as MRI has proven effective in detecting new or recurrent lesions in the prostate. Recently, scoring systems have been developed to evaluate post-focal treatment MRIs, in which the likelihood of recurrent disease is scored.^22 23^ These systems offer guidance on subsequent steps, ranging from continued observation to additional diagnostic procedures such as biopsies. We will implement such a scoring system (PI-FAB scoring system) alongside standardised biopsies at 1-year follow-up to confirm the presence or absence of a tumour after focal treatment. This approach allows us to validate the scoring system by comparing its outcomes with biopsy results.

Third, QoL will be assessed using patient-reported questionnaires, which may be subject to bias such as recall bias and response bias. These questionnaires are, however, validated, and the use of these questionnaires aims to reduce these biases.

In conclusion, this ongoing RCT aims to contribute to the evidence needed to define the role of focal therapy in the treatment of intermediate-risk PCa, despite persistent methodological and clinical challenges.

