## Methods

### Design

ENFORCE focal is a pragmatic multicentre, RCT comparing the (cost-)effectiveness of focal therapy to radical whole-gland treatment, that is, RP or RT, in patients with intermediate-risk PCa. Patient recruitment will be performed in outbound patient clinics in six Dutch centres and their networks. Each participating centre performs a focal ablation technique and radial whole-gland treatment. Focal therapies applied in the study are TULSA, HIFU and IRE; each centre performs one of the focal therapies. Radical treatment will be performed as per normal routing. This means that RP will be performed by the urologist in the participating centres or in their collaborative network, and patients choosing RT will be referred to RT centres. Within the trial, one of the participating centres collaborates with a dedicated HIFU clinic where the focal treatment is carried out. Follow-up will be at least 3 years, with a maximum of 5 years to gain information regarding long-term outcomes. The set follow-up visits are 6 weeks, 3 months, 6 months, 12 months and yearly thereafter. At the follow-up visits clinical data will be collected, and questionnaires regarding QoL and costs will be administered. Furthermore, at 9 months and 18 months PSA will be monitored in both groups in alignment with European guidelines on follow-up after RP and RT. For the focal therapy arm, at 12 months, an MRI and prostate biopsies will be performed. In the years thereafter, a prostate MRI will be performed yearly with additional biopsies on indication, such as rising PSA levels over time, suspicious MR findings in the treated zone or newly identified lesions outside the treated area.

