### Randomisation

Eligible participants who provide informed consent will be randomised in a 1:1 ratio to focal therapy or radical whole-gland treatment using a computer-generated allocation sequence. Randomisation will be stratified by centre, Gleason score (3+4 or 4+3) and age group to ensure balanced distribution of participants across treatment arms within each stratum.

Random block sizes will be used within each stratum to maintain allocation concealment. The allocation sequence will be implemented via a centralised web-based system to maintain blinding of investigators and study personnel involved in enrolment.

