### Interventions

The therapies within the intervention group are HIFU, TULSA and IRE. If a patient is assigned to focal therapy, the treatment a patient receives is based on the centre where the inclusion took place. This means that a patient is not able to choose what kind of focal therapy will be received in case of randomisation for focal therapy. The control group consists of RP or RT. If a patient is allocated to radical treatment, the patient will receive treatment as per current clinical practice in the Netherlands according to the Dutch guidelines. For RP, different types of approaches are possible, including nerve-sparing and non-nerve-sparing options, depending on tumour characteristics and anatomical considerations. Patients receiving RT will be treated as per national guidelines. Therapies administered can include RT with hypofractionation (28 fractions with 2.5 Gy, total dose of 70 Gy or 20 fractions with 3.1 Gy, total dose of 62 Gy) and RT with ultrahypofractionation (5 fractions with 7.25 Gy, total dose of 36.25 Gy). All RT regimens provide bio-equivalent doses similar to conventional RT consisting of 35 fractions with 2 Gy. According to the current national guidelines, the addition of androgen deprivation therapy (ADT) is not recommended for patients with intermediate-risk PCa with a PSA level of 20 ng/mL or lower. Patients eligible for both RP and RT are provided with evidence-based information, including a decision aid, to support shared decision making. The final treatment choice is made jointly by the patient and the urologist.

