### Recruitment

Patients will be recruited from the six participating centres and their regional networks. Two of the including centres will perform TULSA, two will perform IRE and two centres will perform HIFU. One of the centres that performs HIFU collaborates with the including hospital in which the usual care arm will be performed.

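### Each focal modality can be compared with radical treatment with centre adjustment; the Discussion's statement that this is impossible holds only for contrasts between focal modalities

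*Protocol article*

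**What the plan says.** All references are to the protocol article.

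- Discussion, first expected challenge: to learn about possible differences between modalities, "we will perform exploratory analyses for the focal therapies versus the radical treatments". The next sentence says "Adjustment for centre will not be possible in these analyses since the type of focal therapy is centre-dependent" and adds, as a second reason, that the standard-of-care options on offer are not the same in every centre.
- Design: "Each participating centre performs a focal ablation technique and radial whole-gland treatment", and "each centre performs one of the focal therapies".
- Interventions: for a patient assigned to focal therapy, "the treatment a patient receives is based on the centre where the inclusion took place".
- Recruitment: "Two of the including centres will perform TULSA, two will perform IRE and two centres will perform HIFU".
- Randomisation: participants "will be randomised in a 1:1 ratio to focal therapy or radical whole-gland treatment", and "Randomisation will be stratified by centre, Gleason score (3+4 or 4+3) and age group".

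The article does not say whether each modality is to be compared with the radical patients of its own centres or with those of all six.

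**The concern.** The sentence in the Discussion rules out centre adjustment for the comparison named just before it, focal therapies against radical treatments. The reason given, that modality depends on centre, prevents adjustment only when focal patients are compared with one another. For a modality against radical treatment, the design supplies both arms inside every centre.

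This matters because the analysis plan is still to be finalised. Its authors would read in the published protocol that the within-centre analysis cannot be done. If they then compared each modality, unadjusted, with the whole radical arm, the result would mix the modality's effect with differences between centres in case mix, in the split between prostatectomy and radiotherapy (which have different PSA failure criteria under Primary endpoints), and in perioperative practice.

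**Working it through.** The disputed statement carries no figure to reproduce. The check has three parts: whether the effects can be estimated, how large the bias would be under a pooled comparator, and what the within-centre comparison costs in precision.

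**1. Can the effects be estimated with centre in the model?**

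Inputs: six centres, one modality per centre, two centres per modality (Design, Recruitment); both arms randomised in every centre (Randomisation).

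- Modality against radical treatment: there are 6 × 2 = 12 centre-by-arm cells. A model with 6 centre effects and 3 modality-versus-radical effects has 9 columns, and its rank is 9. All three effects are estimable with centre adjustment.
- Focal patients only: there are 6 cells. Six centre effects and three modality effects again make 9 columns, but the rank is 6. Modality is nested in centre, so it cannot be separated from centre here.

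The statement is therefore wrong for the first comparison and right for the second.

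**2. Bias if the comparator were all six centres, unadjusted**

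Let *p*_own be the radical-arm failure rate in a modality's two centres, *p*_rest the rate in the other four, and *d* the true focal-minus-radical difference in the modality's own centres. With equal recruitment (an assumption), two of six centres supply one third of the pooled radical arm:

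- pooled control rate = (1/3) *p*_own + (2/3) *p*_rest
- expected estimate = (*p*_own + *d*) − pooled rate = *d* + (2/3)(*p*_own − *p*_rest)

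The documents give no failure rates by centre, so the gap is an assumption, shown as a range:

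- gap 0: bias 0
- gap 5 points: (2/3) × 5 = 3.3 points
- gap 10 points: (2/3) × 10 = 6.7 points

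For scale, the difference anticipated in the Sample size section is 5 points.

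A simulation agrees (4,000 runs, 356 patients, true difference 5.0 points in every centre, assumed radical failure rates of 8, 12, 15, 15, 20 and 20% in the six centres). Mean estimates for the three modalities, in points:

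- against all radical patients: 0.1, 5.2, 9.9
- against own-centre radical patients, unadjusted: 5.0, 5.1, 4.9
- against own-centre radical patients, stratified by centre (Mantel-Haenszel weights): 5.0, 5.1, 4.9

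With uneven centre sizes the pooled comparison gives −0.1, 5.8 and 10.8, and the stratified one 5.0, 4.9 and 5.0. The last two analyses coincide because allocation was exactly 1:1 within each simulated centre.

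**3. Precision**

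With equal recruitment, 356/6 ≈ 59 patients per centre. Two centres split 1:1 give about 59 focal and 59 radical patients per modality; the pooled radical arm has 356/2 = 178. The failure rates (radical/focal) are assumptions, since the article states only the 5-point difference.

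At 15%/20%, the variance terms are 0.15 × 0.85 = 0.1275 and 0.20 × 0.80 = 0.16:

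- own centres: √[(0.16 + 0.1275)/59] = 0.0698, or 7.0 points
- pooled: √[0.16/59 + 0.1275/178] = 0.0586, or 5.9 points

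At 10%/15%:

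- own centres: √[(0.1275 + 0.09)/59] = 6.1 points
- pooled: √[0.1275/59 + 0.09/178] = 5.2 points

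At 20%/25%:

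- own centres: √[(0.1875 + 0.16)/59] = 7.7 points
- pooled: √[0.1875/59 + 0.16/178] = 6.4 points

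The within-centre interval is thus a little under to about one fifth wider (at 15%/20%, 0.0698/0.0586 = 1.19).

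**The case against.** The strongest reply is that no pooled comparator is stated. A reader might infer from the sentence that each modality will be set against radical patients from all six centres and that the planned analysis is therefore confounded. The documents do not support that: they leave the comparator open, and with own-centre controls the unadjusted estimate is essentially unbiased. This part of the reply stands, and the bias figures are conditional for that reason.

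Second, the stated aim is to learn about differences between modalities, and for direct contrasts between them the caveat is correct. The passage also warns openly about differing standard care and perioperative practice. This stands too, but the sentence as written refers to focal therapies against radical treatments, where it is wrong.

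Third, the radical treatments may mean prostatectomy and radiotherapy taken separately. A centre might then lack one of them, and the choice between them is made by patient and urologist, not by randomisation. That limits any split by radical option; stratifying by centre does not repair it. It does not prevent comparison with the radical arm as a whole.

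Fourth, the collaboration of one including centre with a separate HIFU clinic might seem to break the within-centre comparison. It does not: the including centre fixes the modality, and usual care is delivered at the including hospital.

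Finally, these analyses are exploratory, do not appear in the Analysis section, and lie outside the main comparison of groups of therapies. A reader might infer that reimbursement of a single device hangs on them. The Discussion links the trial as a whole to reimbursement, but nothing ties that decision to these contrasts.

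**Conclusion.** The statement that centre adjustment is impossible is wrong for each focal modality against radical treatment and right for contrasts between modalities. This follows from the design alone and needs no assumption about rates.

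Any bias depends on a choice that the article does not state. It arises only with an unadjusted comparator pooled over centres, and then in proportion to a between-centre gap that the documents do not quantify. With own-centre controls, what is lost is use of a factor by which the randomisation was stratified.

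The point concerns exploratory analyses only, and neither co-primary conclusion changes. It is worth correcting because the sentence steers the analysis plan away from a randomised comparison that the trial already provides.

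**What to change.** Replace the sentence in the Discussion, and carry the same text into the analysis plan:

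> Each focal modality is compared with the radical-arm patients randomised in the same centres, stratified by centre. Differences between modalities, whether direct contrasts or a modality-group × arm interaction, remain mixed with between-centre differences (two centres per modality, differing RP/RT mix and perioperative practice) and are descriptive only.

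The second sentence is needed because stratifying by centre does not make the modality effects comparable with one another: with two centres per modality, the interaction also absorbs differences between centres in treatment effect.

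The change is one of wording and needs no new data. Its price is the wider interval shown in the working, relative to pooled controls.

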### Trial status

Recruitment started in January 2024 with the first patient being included in February and is currently ongoing in six centres. A total of 110 patients are enrolled in October 2025, and we expect to need 2.5 years in total for the inclusion of 356 patients. A 1-year follow-up regarding QoL is expected for the whole group at the end of 2027. For the oncological effectiveness, the 3-year follow-up is expected at the end of 2029.

### Focal therapies

#### Transurethral ultrasound ablation

TULSA is a treatment in which a prostate tumour is treated with US under MR guidance. For this procedure, patients receive general anaesthesia. Afterwards, a patient will be positioned on the MR table. The transurethral device (UA) is inserted into the prostate, and the rectal cooling device is placed inside the rectum. The UA has 10 US elements which can individually provide energy. After positioning the patient and device, MR imaging is performed. Treatment planning is performed by the clinician and the TULSA system. Since the TULSA will be a focal approach, a partial gland ablation will be performed. After the procedure, a post-ablation scan will be performed to determine the treated area. If the treatment has been performed to the satisfaction of the clinician, the device will be removed and a catheter will be placed. Patients will be admitted for one night. They will be discharged from the hospital if in good clinical condition the day after.

#### Irreversible electroporation

IRE is an US-guided treatment. In this treatment, patients will receive general anaesthesia and muscle relaxation. After induction, patients will be positioned in the lithotomy position. Needles are then transperineally placed with the use of a transrectal US. By using a grid, the needles will be placed around the tumour. After placement, pulsatile high-voltage electric currents will be run between the needles in pulses. These pulses generate an electric field that permeabilises the cell membranes within the treatment zone and thus includes the tumour cells. The formation of irreversible nanopores in the cellular membrane leads to a disruption of the cell membrane, resulting in cell death. Periprocedural imaging with US and the planning software of the IRE help in ensuring complete coverage of the area of interest. A catheter will be placed during the treatment, and patients will be discharged from the hospital the same day or after 1 day if in good clinical condition.

#### High-intensity focused ultrasound

HIFU is an US-guided treatment while using HIFU to treat a prostate tumour. Patients receive spinal anaesthesia with sedation for this treatment. After the anaesthesia is performed, a catheter is placed, and patients will be positioned in the right lateral decubitus position. After positioning, the endorectal device is inserted. The diagnostic MRI is fused with real-time US imaging for treatment planning. After the fusion, the HIFU device performs the treatment planning. After planning, the ablation will be performed using real-time US guidance. This is also used to determine the treated area is sufficient for the treatment of the lesion of interest. If patients are in good clinical condition, they will be discharged the same day as the treatment takes place.
